## Abstract

**Background:**

Tobacco use is the largest preventable cause of death. Smoking cessation interventions that use implementation intentions show promising results. Implementation intentions are if-then plans that specify a certain behaviour within a situational context. This study will examine whether involving a non-smoking partner could improve planning interventions, and whether and which partner interactions underlie this effectiveness.

**Methods:**

This single-blind randomized controlled trial has a longitudinal design with a baseline questionnaire, end-of-day measurements for three weeks starting on the quit date, and a follow-up questionnaire after three months.

Participants: single-smoking couples who live together and are in a relationship for more than one year.

Setting: couples are randomized to either a dyadic or individual planning condition. After the intervention the smoker attempts to quit smoking and the diary measurements start.

Measurements: The primary outcome variable is smoking abstinence. Secondary outcome measures are smoking behaviour and relationship satisfaction. Partner interactions are examined as a possible mediator.

**Discussion:**

This RCT is the first to examine the effectiveness of dyadic planning to quit smoking in single-smoking couples. Partner interactions are thought to play an important role during the quit attempt, and therefore in the effectiveness of the intervention. This RCT will provide more insight into which daily partner interactions are beneficial for smoking abstinence and the couples’ relationship satisfaction, and whether the type of intervention is related to different types or levels of partner interactions and smoking behaviour. When proven effective, this planning intervention in combination with coaching for the non-smoking partner will be a valuable and low-cost addition to existing smoking interventions.

**Trial registration:**

The trial is retrospectively registered on 19/04/2017 on www.trialregister.nl (TC: 6398).

**Electronic supplementary material:**

The online version of this article (10.1186/s40359-018-0266-8) contains supplementary material, which is available to authorized users.

## Background

Despite discouraging measures and intervention programs to help individuals to quit smoking, the percentage of smokers in the Netherlands is still about 24% [1]. With tobacco smoking as the largest preventable cause of death [2], successful smoking cessation interventions are important. The use of implementation intentions seems a promising method to help smokers to quit [3]. This RCT examines whether involving a non-smoking partner could improve planning interventions, and whether and which partner interactions underlie this effectiveness.

Implementation intentions are if-then plans that specify a certain behaviour within a situational context [4]. These intentions show enduring changes in behaviour and therefore increase the likelihood to achieve one’s goals. An example of an implementation intention is: “After dinner when I crave a cigarette, I’m going for a walk instead of smoking a cigarette.” Planning interventions (in which implementation intentions are formed) are in general effective in changing health behaviour [5], and it shows promising results for smoking behaviour [3]. Specifically, forming if-then plans (e.g., of what to do when one has cravings or when one is in a situation where one usually smokes) has been found to decrease smoking habits (i.e. smoking automatically without thinking about it) and the number of cigarettes smoked in a group of current smokers.

To enhance the efficacy of implementation intention interventions, involving the spouse could be beneficial [6]. The health behaviour of a spouse is an important influencing factor of one’s own health behaviour, including smoking [7]. Research shows that smokers partnered with a non-smoker (i.e. single-smoking couples), compared to those partnered with a smoker, more often try to quit [8, 9], use less tobacco [10] and have an increased likelihood of (successful) smoking cessation [11]. Approximately 35% of the smokers have a non-smoking partner [11, 12]. Additionally, non-smokers, compared to smokers, are more willing to support their partner’s quit attempt and to use influence tactics such as complimenting on not smoking or criticizing smoking behaviour [13]. This intended support is even higher when partners are more satisfied with their relationship*.* Receiving partner support seems an important contributing factor to successful smoking cessation. When smokers bring a support partner to a smoking cessation therapy, the abstinence rate is significantly greater and more likely to be sustained for at least one month [14]. Support from a non-smoking partner, both prior to and during a self-set quit attempt, was related to less smoking [15]. After the quit date, when support is needed the most, changes in support were even stronger related to changes in number of cigarettes smoked. All in all, one could say that smokers who are in a single-smoking relationship are in a favourable social environment to quit smoking. The next step is to examine how this favourable environment can be used to help the smoker to quit.

In our RCT, we aim to involve the non-smoking partner before the quit date by asking the couple to jointly create an if-then plan for the smoker to quit smoking. This would change the role of the partner from just a support provider to a part of the team: quitting smoking becomes a dyadic effort. In dyadic planning, the partner can help by thinking of and supporting plans such as how to resist the temptation of smoking a cigarette. We will examine the effect of dyadic planning to quit smoking in comparison to individual planning, where the smokers make a plan on their own.

Research on dyadic planning is limited. To the best of our knowledge, there are no studies focusing on dyadic planning to quit smoking. Dyadic planning has been studied in the context of implementing a new (health) behaviour. However, it did not help to involve the partner in planning to increase daily physical activity in target persons and their partners [16], nor to integrate pelvic-floor exercise in daily life after prostatectomy [17]. On the other hand, dyadic planning (compared to individual planning) was more successful regarding maintenance of these exercises [18]. Therefore, dyadic planning might be a promising method to prevent relapse. Dyadic planning also seemed to buffer the detrimental effects that negative control of the partner had on behaviour change [17]. Perhaps the controlling behaviour of the partner feels justified because the couple is operating as a team; social control might be perceived differently.

Several aspects might explain why no intervention effects were found. As the authors state, dyadic planning might occur in all couples as a general adjustment strategy after surgery [17], so partners could have involved themselves in the planning in both conditions. Dyadic planning failed to increase physical activity in target persons and their partners in daily life [16]. Although this study had a target person that was the focus in the planning, this target person was randomly chosen within the couple and the plans could apply to both partners. Accordingly, increased activity was expected in both partners: the partners’ activity was also monitored. This might compromise the measure of the effect of the dyadic planning, since when the partner is not changing his or her behaviour, the target person might be less motivated to do so. In our study, the drafted plans are only applicable to the smoker, therefore creating a different situation within the couple. The target person is clear, and the role of the partner is to help with the plan and to support the smoker.

Collaborative planning has also been studied in the context of implementing a new (health) behaviour and results seem promising. It can be distinguished from dyadic planning, in that the partner is not only involved in creating the plan, but also plays a role in the plan itself (e.g., enacting a behaviour together) [6]. When the partner was involved in creating collaborative implementation intentions to increase physical activity in counsel employees, it was more effective [19]. These participants lost more weight over time and were more physically active then participants who made intentions individually. Since, smoking in single-smoking couples is likely an individual activity, often performed in the absence of the partner, plans have to be created that can be acted upon alone. However, couples are allowed to integrate collaborative plans for times they are together (e.g. taking a walk together or playing a game when the smoker has a difficult moment in the evening). Therefore, the main elements of the intervention lie in the dyadic planning, while collaborative planning may be part of the plan only when the spouses make it so. We therefore consider this a dyadic planning intervention.

Measuring partner support is an important step to fully understand the effectiveness of and working mechanisms behind a dyadic and individual planning intervention. Therefore, in our RCT partner support that occurs naturally in both conditions will be examined (Fig. 1). The nature of support for the smoker does matter. A greater frequency of supportive behaviours of the partner predicts cessation attempts [20], while negative behaviours such as criticizing, nagging and policing in relation to smoking are impediments to smoking cessation [21]. The nature of support can fluctuate during the course of a quit attempt. During moments of relapse, the likelihood of negative support increases and the smoker is perceived as less committed to quitting smoking by their partner [22]. Also, quitting increases anger, irritability and frustration in smokers [23], which might trigger conflicts between spouses. Dyadic planning might act as a buffer for negative behaviours [17]. When the non-smoking partner is involved in creating implementation intentions, quitting smoking becomes more a dyadic effort than an individual effort. Support might be different or perceived as different when the couple is operating as a team, compared to when one partner of the couple is working on the task alone. This might explain why dyadic planning can act as a buffer for negative behaviours while individual planning does not show this effect [17]*.* So, dyadic planning could be more effective for successful smoking cessation, because it influences the provided support and behaviour of the partner, or the perception of these responses, or both.

**Fig. 1 Fig1:**

The proposed model with partner interactions as a mediator

### Aims of the present study

The primary aim of this study is to assess immediate effectiveness and effectiveness over time of a dyadic planning intervention compared to an individual planning intervention for smoking cessation in smokers with a non-smoking partner. We hypothesize that participants in the dyadic planning condition will report fewer cigarettes smoked and a longer duration of abstinence than participants in the individual planning condition. We also hypothesize that participants in the dyadic planning condition will report higher relationship satisfaction than participants in the individual condition.

The secondary aim of this study is to examine possible underlying mechanisms in effectiveness in terms of partner interactions. We will examine differences between the conditions in the nature and frequency of partner interactions and how they are related to daily smoking behaviour and relationship satisfaction. We hypothesize that partners in the dyadic condition show more supportive behaviours in general and after a weak moment (of relapse), more often discuss weak moments, the plan, and the quit attempt. Additionally, we hypothesize that negative responses of the partner in the dyadic condition are less strongly related to a decrease in relationship satisfaction than in the individual condition.

## Methods

### Participants

Participating couples must consist of one smoker (smoking cigarettes every day or multiple days per week) and one non-smoker, who are in a relationship for at least one year and living together. Both partners should have their own mobile phone, for receiving the daily questionnaire. Exclusion criteria are pregnancy and aged younger than 18. Participants from the Netherlands can enroll from April 2017 to July 2018.

### Procedure

This single-blind randomized controlled trial has a longitudinal design with a baseline questionnaire, measurements once a day for three weeks, and a follow-up questionnaire after three months (Fig. 2). Participants are recruited using social media (e.g., Facebook, Twitter), by repeatedly posting a short advertisement with a link to the website [24]. Facebook appears to be an effective channel to recruit single-smoking couples [25]. When couples want to participate, they can fill in an application form on the website, which asks for both members’ e-mail addresses and their smoking status. The applications are organized in an encrypted file, where they are randomly assigned to either the individual or dyadic condition, and receive a respondent number and couple code. Participants can stop participating at any time upon request.

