#### Baseline (T0)

A message will be sent to the e-mail addresses participants provided through the website. This e-mail contains information about every part of the study, participation and privacy regulations. Every participant will get a personalized link to the baseline questionnaire (T0), where participants give their informed consent. At the end of this survey, participants will be asked to fill in their home address and phone number. These data will be added to the encrypted file with participant information. Then, a package will be sent to the given address, containing an information letter, an instruction manual with frequently asked questions (FAQs) about the diary period, and a closed colored envelope. This envelope contains either a blank individual or a dyadic planning sheet.

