### Randomization

Couples are randomized by the researchers by means of flipping a coin. Conditions are predetermined (before registration of the couple) by this method for every block of ten couples, to exclude any kind of influence the researchers might have. The randomization is single-blind; couples do not know that there are two different conditions until the debriefing that is given after the follow-up questionnaire. When participants do not fill in the follow-up questionnaire, the debriefing is sent to them by e-mail.

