### Statistical analyses

For our primary aim we will compare the proportion of successful abstainers in both groups, weekly (day 7, 14, 21) and after 3 months (primary outcome variable). Primary analyses are conducted with baseline and follow-up data according to the intention-to-treat approach. Secondly, we will compare the number of cigarettes smoked between the groups, controlling for baseline smoking (secondary outcome variable). Similar comparisons will be made for relationship satisfaction (secondary outcome variable). Additional independent and paired post-hoc t-tests will be performed to examine between-group and within-group differences, and chi-square tests for categorical variables*.* For the secondary aim, we will examine the effects of partner interactions on same and next-day smoking behaviour and relationship satisfaction (concurrent and lagged effects). Multilevel modelling will be used to analyse the diary data [29]. The diary data is nested within individuals and couples. Multi-level analyses will take into account between-person variation (individual variation from the grand mean) as well as within-person variation (an individual’s daily variation from their personal mean). To examine the indirect effect of the intervention on smoking and relationship satisfaction via partner interactions, we will conduct a within-person mediation analysis, allowing for random intercepts and slopes [29]. We will check whether the randomization was successful regarding demographical, smoking and relationship variables. If not, those variables will be taken into account as covariates in the analyses. 

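### Couples are assigned at application, before consent, baseline and most described eligibility checks, which conflicts with the stated intention-to-treat analysis and lets early losses erode the sample

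*Protocol article*

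**What the plan says.** All references are to the protocol article.

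- **Procedure.** Couples apply through the website on a form "which asks for both members’ e-mail addresses and their smoking status". Then: "The applications are organized in an encrypted file, where they are randomly assigned to either the individual or dyadic condition". They receive a respondent number and couple code at the same step.
- **Baseline (T0).** The study e-mail goes out afterwards: "Every participant will get a personalized link to the baseline questionnaire (T0), where participants give their informed consent". Home address and phone number are collected at the end of T0, and the package with the closed envelope is posted after that.
- **Participants.** Couples must be ones "who are in a relationship for at least one year and living together", and each partner needs a mobile phone. "Exclusion criteria are pregnancy and aged younger than 18". None of these items is mentioned as part of the application form.
- **Randomization.** The researchers allocate by coin flip and do so ahead of time: "Conditions are predetermined (before registration of the couple) by this method for every block of ten couples"; the stated purpose is to keep the researchers from affecting the allocation. Couples learn that there are two conditions only at debriefing.
- **Statistical analyses.** "Primary analyses are conducted with baseline and follow-up data according to the intention-to-treat approach".
- **Power analysis.** 70 couples per group, from 15% abstinence in the control group, an increase of 20%, power 0.8 and alpha .05. A further 15% of couples are to be included for drop-out.

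**The concern.** Read in order, these sections randomise couples who may turn out to be ineligible, may not consent or may never complete T0. Two things are at stake.

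The first is the analysis set. An intention-to-treat analysis takes couples as randomised, but those lost before T0 have no baseline data and probably no follow-up data. Dropping them means the set is no longer all randomised couples. Keeping them means the named data do not exist for them. The losses also draw on a reserve that was presumably meant for drop-out during the study.

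The second is knowledge of the arm. The researchers make the sequence, and the assignment is recorded in the application file. Fixing the list early protects the sequence from being altered. It does not by itself stop someone who knows a couple's arm from influencing whether that couple proceeds through T0 and eligibility, and no step that would prevent this is described.

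**Working it through.** **Order of steps as written**

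1. The sequence is made by coin flip before couples register (Randomization).
2. The application gives e-mail addresses and smoking status (Procedure).
3. The condition is assigned in the application file (Procedure).
4. Consent and baseline questionnaire, T0 (Baseline).
5. The envelope is posted (Baseline).
6. The intervention is given by phone, and the diary starts the next day (Intervention and diary period).

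Nothing described between steps 3 and 5 needs the assignment.

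**Reproducing the planned size**

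Inputs from the Power analysis section: p1 = 0.15, p2 = 0.35, power 0.80, alpha 0.05 (taken as two-sided). The 20% is read as percentage points, because a relative increase (15% to 18%) would need 2402 per group.

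n per arm = (1.960 + 0.842)² × [p1(1−p1) + p2(1−p2)] / (p2−p1)² = 7.849 × (0.1275 + 0.2275) / 0.04 = 69.66, so 70. The planned figure is reproduced.

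**Power formula used below** (pooled variance under the null, with p̄ = 0.25)

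Power = Φ{ [0.20 − 1.96·√(2 × 0.25 × 0.75 / n)] / √(0.355 / n) }

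At n = 70: (0.20 − 0.1435) / 0.0712 = 0.794, so power is 0.786. This is the comparator for what follows.

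**Loss before T0**

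Planned couples: 140 × 1.15 = 161. Assumption 1: these are counted at assignment. Assumption 2: a proportion L is lost between assignment and completed T0. The article gives no value for L, so a range is shown. Couples remaining = 161 × (1−L).

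| L (assumed) | Couples left | Power, no later loss | Power, further 15% later loss | Power if all 161 are analysed and those lost before T0 count as smoking |
|---|---|---|---|---|
| 0% | 161 | 0.84 | 0.78 | 0.84 |
| 10% | 145 | 0.80 | 0.73 | 0.79 |
| 20% | 129 | 0.75 | 0.68 | 0.72 |
| 30% | 113 | 0.69 | 0.62 | 0.65 |
| 40% | 97 | 0.63 | 0.55 | 0.57 |
| 50% | 81 | 0.55 | 0.48 | 0.48 |

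The last column uses n = 80.5 per arm and rates of 0.15(1−L) and 0.35(1−L), with no later loss.

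The reserve is used up when 161 × (1−L) = 140, that is L = 21/161 = 13%. The first row is what assignment after T0 would give.

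**Arm-aware selection (illustration only)**

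Suppose there is no true effect, abstinence is 15%, 70 couples per arm are analysed, and a fraction d of couples with no chance of quitting is dropped from the dyadic arm only. The observed dyadic rate becomes 0.15/(1−d). With d = 10% it is 16.7% and the type I error is about 0.058. With d = 20% it is 18.7% and the type I error is about 0.091. Nothing in the article suggests that such selection occurs.

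**The case against.** A reader might infer that the intention-to-treat analysis is impossible. The documents do not support that. Couples are unaware of the two conditions until debriefing, and they receive nothing arm-specific until after T0, so their own early withdrawal should not depend on arm. Leaving those couples out mainly costs precision and can be defended as a modified intention-to-treat set, provided staff do not select who proceeds. All randomised couples could also be analysed with early losses counted as smoking. Moreover, the reference to baseline and follow-up data may simply separate the questionnaires from the diary, and the proportion abstinent does not itself need a baseline value. All of this stands. It still leaves the article without a set of couples that fits both its enrolment order and its named analysis.

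A reader might also infer that allocation is not concealed. That would be an inference from silence. No passage says that whoever handles applications sees the next assignment, and self-application through a website with online consent limits steering into an arm. What can be said is that no concealment step is described and that the arrangement makes the arm knowable before T0. Knowledge of the arm after T0 is a different matter: whoever makes the intervention call must know it under any scheme.

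The phrase about eligibility also needs care. Smoking status, the defining criterion, is on the form, and a one-clause summary of the form need not list every field. Fig. 2, the participant timeline, is not shown in the text reviewed and could bear on the order of steps.

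Finally, coin flips might be taken as a defect because they do not balance blocks of ten. Simple randomisation is valid, and the article does not claim balanced blocks. A 64 to 76 split has an effective size of 2 × 64 × 76 / 140 = 69.5 per arm against 70. No point is made of this here.

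**Conclusion.** The concern holds in a limited form. As written, assignment precedes consent, baseline and most described eligibility checks, and this does not fit an intention-to-treat analysis on baseline and follow-up data. The consequence is mainly lost power, plus some risk of selection by staff who could know the arm.

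The size depends on two assumptions: that the 161 couples are counted at assignment, and the unknown pre-T0 loss. At 10% loss power is 0.80, no worse than the 0.786 that the same formula gives for the planned 70 per arm. At 20% it is 0.75, a drop of about 0.04 from that comparator. At 50% it is 0.55. Any loss above 13% leaves no reserve for later drop-out. If the 161 are counted only after T0, this power loss does not arise, but the question of which couples form the analysis set remains.

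This is worth correcting because the remedy is so cheap. It does not invalidate the primary comparison.

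**What to change.** - Assign the condition only when both partners have completed T0 (consent, eligibility, baseline), just before the envelope is posted.
- Keep the next assignment hidden from staff who handle applications, T0 and eligibility until that moment, and state who holds the list.
- Define the intention-to-treat set as all couples randomised at that point, and count the 161 from there.
- For couples already assigned at application, report losses before T0 by arm, with reasons, and call the analysis set modified intention-to-treat.

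The cost is a short procedural amendment and a change to when the list is opened. No extra visits or participants are needed, and since the envelope already goes out after T0, couples would notice no difference.
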